### Randomization

The study participants will be randomized 1:1 into the intervention group (*n* = 101) and control group (*n* = 101). A random sequence will be generated in an Excel spreadsheet, followed by the use of the Excel RAND function-random number-sort. The COMW in the intervention group will be notified of the date and place of the intervention.

### Intervention group

The participants randomly assigned to the intervention group will receive health education, help to schedule screening appointments, navigation services, counseling, and follow-up care from the patient navigators. Regarding health education, each patient navigator will deliver a one-time group education session for 13 COMW (19–23, 28) that will last for 6 h (21, 28). The education session will be interactive and conducted using a PowerPoint, projector, and flipchart to help the COMW understand the content clearly (18–23, 25, 29). During the education session, free drinks will be given to the COMW to make them feel comfortable. The education session will have 4 sessions within the 6 h, whereby session 1, scheduled for 1 h, will be an opening session that allows everyone to introduce themselves and the objective and logistics to be communicated. Session 2 is scheduled for 1 h to cover female reproductive organs and session 3, scheduled for 2 h, is an introduction to cervical cancer, including the cause, risk factors, signs, and symptoms of cervical cancer. Session 4 is scheduled for 2 h to cover the preventive measures for cervical cancer. Please refer to Table 2 for further details. After delivering this one-time health education to the COMW, the patient navigators will begin to provide navigation services during follow-ups, such as scheduling screening appointments, escorting the women to the screening center, taking care of the mother's child, encouraging participants to attend the screening centers for their appointments, and counseling to those who fail to attend the screening center for their appointment.

**Table 2 T2:** Session plan for delivering health education to community women.

Session	Time	Contents
Opening session	12:00–13:00	Welcome of participants
		Introduction of facilitators and learners
		Objectives and overview of health education
		Ground rules and other logistics during health education
Session 2: Understanding the female genital organs	13:00–14:00	What are external female genital organs?
		What are internal female genital organs?
		How does a cervix look during a naked-eye examination?
Discussion		
Session 3: Introduction to cervical cancer, including its causes, risk factors, signs, and symptoms	14:00–16:00	What is cervical cancer?
		What causes cervical cancer?
		What are the risks for cervical cancer?
		What are the signs and symptoms of cervical cancer?
Discussion		
Session 4: Learning about the prevention of cervical cancer	16:00–18:00	What are ways to prevent cervical cancer?
		Who should be screened for cervical cancer?
		What are the common cervical cancer screening tests?
		Where can screening services be accessed?
		What preparation is necessary before a woman goes for a screening test?
		Importance of screening for cervical cancer
		How frequently should a woman be screened for cervical cancer?
		Do women feel any discomfort during screening tests?
Discussion		
Closing	18:00	

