#### Sample size determination of COMW

The sample size for the COMW has been calculated through G-Power software (42) and is based on the outcome variable of completion of screening at a 6-month follow-up. Using the F-test, with an effect size of f = 0.3, α err prob = 0.05, and power (1 − β err prob) = 0.83, the sample size of community women to be recruited will be 202 (intervention group = 101 and control group = 101).

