### Analysis

All data will be entered and analyzed in SPSS version 21 software. To analyze the data from CHWs before and after their training, frequency and proportion will be used for the categorical variables and means for the continuous variables. Changes in knowledge, attitude, health beliefs, and screening intention will be analyzed using the independent sample *t*-test and linear regression.

The data from the COMW at baseline, 3-month follow-up, and 6-month follow-up will be analyzed using descriptive statistics (frequency and proportion), the independent sample *t*-test, linear regression, and a repeated measures ANOVA. Furthermore, principal components analysis (PCA) will be used to identify the frequency (*N*) and percentage (%) of respondents with awareness, knowledge, subjective norms, perceived behavioral control, and health beliefs regarding cervical cancer and CCS.

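### Only the intervention arm is taught in groups and followed by a few navigators, yet the sample size and the named tests treat all 202 women as independent; if outcomes vary by session or navigator, the standard error is too small

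*Protocol article*

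**What the plan says.** Under Randomization, individual women are allocated 1:1, 101 per arm. Under Intervention group, "each patient navigator will deliver a one-time group education session for 13 COMW"; afterwards the navigators arrange appointments, accompany women to the screening centre, mind children, encourage attendance and counsel those who miss appointments. Under Control group, the comparison is usual care, with no sessions and no navigators.

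The Sample size section says the calculation "is based on the outcome variable of completion of screening at a 6-month follow-up". Its inputs are an F-test "with an effect size of f = 0.3", alpha 0.05 and power 0.83, and it concludes that "the sample size of community women to be recruited will be 202". It states no ICC, design effect or cluster size.

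For the women's data, the Analysis section names descriptive statistics, the independent-sample t-test, "linear regression, and a repeated measures ANOVA". None is given a session or navigator term.

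The cluster structure itself is unsettled. The Abstract and the training section have five navigators, while the recruitment section has ten. The Intervention group section has sessions of 13, while the Discussion describes groups of four to eight.

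**The concern.** This is a partially nested design: women in one arm share a session and navigators, and women in the other share nothing. Those who hear the same session, or are followed by the same navigator, may have more similar outcomes than women picked at random. The protocol's own reasoning points that way. The Discussion suggests that women may attend because they expect navigator follow-up, and that pay affects how individual navigators perform.

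Where such similarity exists, 101 intervention women carry less information than 101 independent women. The t-test and linear regression do not allow for it. Repeated measures ANOVA handles correlation within a woman over time, not between women who share a session or navigator. The interval for the effect is then too narrow, for screening completion and for the scale scores alike. With so few clusters, one unusually good or poor navigator could also move the result without the analysis showing it. If session and navigator are not recorded as the trial runs, this may not be repairable later.

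**Working it through.** **The plan's own figure.** With two arms, f = 0.3 and alpha 0.05 (noncentral F, noncentrality f²N), 83% power needs N = 98, and N = 202 gives 98.9% power. So 202 does not reproduce for a two-arm comparison at the stated 0.83. That is a separate defect. What matters here is that no version of the calculation contains a clustering term.

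**Inputs from the protocol article.** 101 women per arm; session size 13 (101/13 = 7.8, about 8 sessions); five or ten navigators; ungrouped controls.

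**Assumed.** ICC 0.01 to 0.10, as the article gives none. Women per navigator, if spread evenly: 101/5 = 20.2 or 101/10 = 10.1.

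**Formulas.** Design effect in the intervention arm: DE = 1 + (m − 1) × ICC. Only that arm is clustered, so the variance of the arm difference is multiplied by V = (DE + 1)/2, and the true standard error is √V times the one computed. The actual two-sided error of a nominal 5% test is 2 × [1 − Φ(1.96/√V)].

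**Example.** Sessions of 13, ICC 0.05: DE = 1 + 12 × 0.05 = 1.60; V = 2.60/2 = 1.30; √1.30 = 1.140; 1.96/1.140 = 1.719; error = 0.086.

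| ICC | Sessions of 13: V | √V | Error | Ten navigators: error | Five navigators: error |
|---|---|---|---|---|---|
| 0.01 | 1.06 | 1.030 | 5.7% | 5.5% | 6.1% |
| 0.02 | 1.12 | 1.058 | 6.4% | 6.1% | 7.3% |
| 0.05 | 1.30 | 1.140 | 8.6% | 7.7% | 10.7% |
| 0.10 | 1.60 | 1.265 | 12.1% | 10.4% | 16.2% |

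A beta-binomial simulation of the two-proportion z-test (40,000 runs, 30% uptake assumed in both arms) agrees. At the same ICCs it gave 5.6%, 6.5%, 8.7% and 11.9% for eight sessions, and 6.1%, 7.3%, 10.8% and 16.2% for five navigators. At ICC = 0 it returned about 5%.

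**Power at the plan's own f = 0.3 (d = 0.6).** Noncentrality is 0.6/√[(DE + 1)/101]. At ICC 0.10 it is 3.37 for sessions (DE 2.20), 3.54 for ten navigators (DE 1.91) and 3.05 for five (DE 2.92). Against 1.96, power is about 92%, 94% and 86%.

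Small-sample degrees of freedom lower this. With k clusters, Satterthwaite df = (DE + 1)²/[DE²/(k − 1) + 1/100], which is 14.6 (k = 8), 20.4 (k = 10) and 7.2 (k = 5). The critical values become 2.14, 2.08 and 2.35, and power becomes about 88%, 92% and 75%.

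**The case against.** Four points can be made against the concern.

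**The inflation is conditional.** A reader might infer that the type I error certainly exceeds 5%. The article does not support that. It gives no ICC, and if the intervention changes no woman's outcome, individual randomisation keeps the test at 5%. Inflation arises when mean outcomes are equal but outcomes vary by session or navigator. This stands, and the conclusion is worded accordingly. It does not remove the problem, because whenever such variation exists the interval is too narrow, whether or not there is an effect.

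**The worst figures rest on an inferred structure.** Twenty women per navigator is stated nowhere, and five navigators with one session of 13 each would reach only 5 × 13 = 65 of the 101 women. Nor does the article say that a woman keeps the same navigator for six months. This stands too: the session of 13 is the best-supported cluster, so its figures lead.

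**The trial may not be short of power.** A reader might infer that clustering leaves it underpowered. At the plan's own f = 0.3 in a two-arm test, power is about 99% under independence and about 86% to 94% at ICC 0.10 before small-sample degrees of freedom. The main harm is to the standard error and the error rate.

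**The article is condensed and an analysis plan may exist.** No test is tied explicitly to the binary primary outcome, and a cluster term could be added to the regression. This helps only in part, because the article itself fixes the sample size and names its tests, all on independence.

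**Conclusion.** The concern holds in conditional form. The intervention arm is clustered by session and navigator, the control arm is not, and the stated sample size and named tests ignore this. For any ICC above zero the standard error of the arm difference is too small. With sessions of 13 it should be 3% to 26% larger over the assumed ICC range of 0.01 to 0.10, and the nominal 5% test of equal mean outcomes runs at about 5.7% to 12.1%. The range is milder with ten navigators and worse with five, the latter only if each has about 20 women.

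These sizes rest on the assumed ICC, on equal cluster sizes and on the normal approximation. No precise design effect can be fixed until the number of navigators and the group size are settled. The article does not support a claim that the error rate is inflated whatever the ICC, or that power is inadequate at its own effect size across the cluster structures. Only the five-navigator case at ICC 0.10, with small-sample degrees of freedom, falls below the stated 83% (about 75%).

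**What to change.** - Record session and navigator for every intervention woman, including any change of navigator, and assign women to them by a recorded rule. Random assignment would be cleanest statistically, but it sits awkwardly with the Discussion's reliance on navigators and women knowing each other. A documented rule, for example by area, is enough if it is recorded.
- Analyse screening completion and the scale scores with a partially nested model: a cluster term in the intervention arm only, each control woman as her own cluster, and small-sample (Satterthwaite-type) degrees of freedom.
- Reconcile the number of navigators (five or ten) and the group size (13 per session against 101 women in the arm, and four to eight in the Discussion).
- Restate power over an assumed ICC range with the settled cluster structure.

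The cost is analysis wording and identifier variables for session and navigator. No extra women are needed to make the analysis valid. Keeping the precision of 202 independent women would take 202 × V, that is 215, 227, 263 or 324 in total with sessions of 13, but that is a separate choice. The downside is wider intervals, few degrees of freedom (about 7 to 20 at ICC 0.10), a variance component that is poorly estimated from so few clusters, and a less favourable stated power.

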### Control group

The participants randomized to the control group will continue to receive the usual care from the national awareness-raising campaign and information from different media, friends, and relatives.

### Data collection and measures

Data will be collected before and after the training of the patient navigators to evaluate whether the training has caused changes in screening knowledge, health beliefs, and skills in providing the intervention. The data will be collected through the adopted questionnaires including those for knowledge and awareness by Khosravi et al. (43), subjective norms by Ogilvie (44), perceived behavioral control by Ogilvie et al. (45), and health beliefs by Ma et al. (46). All the questionnaires are reliable, with acceptable Cronbach's alpha values. For instance, the questionnaire for knowledge, awareness, attitude, and practice has a Cronbach's alpha value ranging from 0.8 to 0.95 on a 3-point Likert scale. The subjective norms questionnaire has a Cronbach's alpha value of 0.83 on a 7-point Likert scale, and the health beliefs questionnaire has a Cronbach's alpha value ranging from 0.75 to 0.88 on a 5-point Likert scale. Please refer to Table 3 for further details. All the questionnaires have been translated into Swahili.

**Table 3 T3:** Measures of the independent variables.

Independent variable	Tool used	Cronbach's alpha	Dimension	Number of items	Scale
(I) Knowledge	Adopted from a previous study (43)	0.92	4	24	3-point Likert scale
Awareness		0.7	1	2	Yes/No
Attitude		0.82	1	9	5-point Likert scale
(II) Subjective norms	Adopted from a previous study (44)	0.91	2	11	7-point Likert scale
(III) Perceived behavioral control	Adopted from a previous study (44)	0.98	1	4	7-point Likert scale
(IV) Health beliefs	Adopted from a previous study (46)	0.76	5	27	5-point Likert scale

The COMW will be assessed for whether the intervention by the patient navigators has changed their screening knowledge, attitude, screening intention, and readiness to utilize screening. The COMW will be assessed by a similar questionnaire that will assess the patient navigators. The data will be collected at baseline (T0), immediately after the intervention (T1), after 3 months (T2), and at the exit at 6 months (T3). The T2 and T3 data collection will be conducted in the households. Finally, the data on whether the participant has been screened or not will be self-reported by the participants and confirmed at the screening facilities.

### Analysis

All data will be entered and analyzed in SPSS version 21 software. To analyze the data from CHWs before and after their training, frequency and proportion will be used for the categorical variables and means for the continuous variables. Changes in knowledge, attitude, health beliefs, and screening intention will be analyzed using the independent sample *t*-test and linear regression.

The data from the COMW at baseline, 3-month follow-up, and 6-month follow-up will be analyzed using descriptive statistics (frequency and proportion), the independent sample *t*-test, linear regression, and a repeated measures ANOVA. Furthermore, principal components analysis (PCA) will be used to identify the frequency (*N*) and percentage (%) of respondents with awareness, knowledge, subjective norms, perceived behavioral control, and health beliefs regarding cervical cancer and CCS.

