### Preparation of the patient navigators

#### Recruitment of potential patient navigators

Patient navigators are defined as the health workforce conducting outreach beyond healthcare facilities or who are based at peripheral health posts that are not staffed by doctors or nurses, who are either paid or volunteers, who are not licensed, and who have fewer than 2 years of training but at least some training, if only a few hours (34). The roles of patient navigators involve community mobilization, health promotion, provision of preventive services, provision of clinical services, epidemographic surveillance, and record-keeping (35). Therefore, non-healthcare professionals who are considered to be potential patient navigators will be recruited into the study through purposive sampling. The recruitment process will involve local community leaders who will propose the potential participants. Participants will be recruited if they are women, residents of the study area (21, 29, 36, 37), have community influence, are well respected in their communities, and have a secondary/high school/university level of education (19, 36). All the suggested participants will be visited by healthcare professionals at their homes to ask about their interests and willingness and further check whether they are eligible. Ten eligible patient navigators will be asked to give their informed consent (19, 24, 26, 29), administered a baseline questionnaire, and invited to participate in the training sessions.

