#### Training patient navigators

The training of five patient navigators will be facilitated by a nurse with a master's degree in oncology nursing who is currently working in the cervical cancer screening department. The training will be conducted using a training manual that is already developed by the principal investigator. The development of the manual has undergone five steps: (i) development of the first draft of the training manual through a systematic review study (38), (ii) revision of the training manual based on the available content in the World Health Organization facilitator guide (39), (iii) revision of the training manual based on a cross-sectional study (40), (iv) revision of the training manual based on an expert's comments, and (v) translation of the training manual from English into Swahili. The theory of planned behavior (TPB) and the health belief model (HBM) were used during the development process.

Patient navigators will receive training on three consecutive days (19, 21, 25, 26, 29, 41) from 9:00 a.m. until the scheduled activities for the day are accomplished (41). A healthcare professional will facilitate the training in Swahili (19, 24, 26, 29). Even after the 3-day training, the healthcare professional will continue to provide ongoing education to enable the patient navigators to acquire more knowledge and skills (21, 24, 29). In the 3-day training, seven sessions will be conducted. The training will begin with a 1-h open session; the patient navigators will be registered and welcomed to the training, followed by a self-introduction from the healthcare professional and the patient navigators. The healthcare professional will clearly state the goal, objectives, and rules of the training. Interactive learning visual aids, discussions, and role-playing will be used throughout the sessions. A PowerPoint (PPT) and projector will be used during the training. The healthcare professionals should prepare marker pens, notebooks, whiteboards, blackboards, and all other required teaching materials. There will be breaks between sessions with free lunches and drinks.

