### Outcome variables

The primary outcome of this study is the completion of CCS within 6 months in both the intervention group and control group (9–36, 39–41). Above 50% will indicate optimal screening uptake. The secondary outcome is the change in the level of knowledge, awareness, intention, and health beliefs toward cervical cancer and screening among the patient navigators and COMW after the training and education sessions (9, 47–50). For group items, >50% will indicate adequate knowledge, positive attitude, positive health beliefs, and being unaware of cervical cancer and CCS. Social demographic characteristics will be assessed to identify their association with the uptake of CCS services.

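### Navigators' scores before and after training come from the same women, but the plan tests the change with an independent-sample t-test

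*Protocol article*

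**What the plan says.** The section on data collection and measures sets the design: "Data will be collected before and after the training of the patient navigators to evaluate whether the training has caused changes in screening knowledge". The section on recruitment of navigators confirms that the first measurement is taken on those about to be trained, who are "administered a baseline questionnaire, and invited to participate in the training sessions". No navigator comparison group appears anywhere in the article.

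The first paragraph of the Analysis section is about these data. It opens "To analyze the data from CHWs before and after their training", names frequencies, proportions and means, and continues "Changes in knowledge, attitude, health beliefs, and screening intention will be analyzed using the independent sample" t-test and linear regression. No paired method is named for navigators. The community women have a separate paragraph, which lists its own independent-sample t-test and a repeated measures ANOVA.

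The Outcome variables section gives these scores formal status: "The secondary outcome is the change in the level of knowledge, awareness, intention, and health beliefs toward cervical cancer and screening among the patient navigators". The same outcome covers the community women.

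The number of navigators is given in two ways. Under recruitment, "Ten eligible patient navigators will be asked to give their informed consent". Under training, "The training of five patient navigators will be facilitated by a nurse"; the Methods part of the Abstract also says five.

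**The concern.** An independent-sample t-test compares the means of two unrelated sets of people. With one group measured twice, the only two samples it can be given are the before scores and the after scores, and each navigator is in both. The independence assumption therefore fails by design.

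Women who score high before training will usually tend to score high after it. That positive correlation makes the mean change more precise than the independent test supposes. The test then uses too large a standard error, its p-values are too large and its intervals cover too often. With five or ten people there is little information to spare, and the plan discards part of it. If the correlation were negative, the error would run the other way and the test would reject too often.

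A linear regression of score on time that treats all the scores as independent has the same fault.

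**Working it through.** **No figure to reproduce.** The article states no sample-size calculation, SD, correlation or expected gain for the navigator analysis. Its only power statement concerns the community women.

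**Inputs.**
- Design: one group, measured before and after (Data collection and measures; Analysis).
- Number of pairs: n = 5 (Training patient navigators; Abstract) or n = 10 (Recruitment of potential patient navigators).
- Assumed here: two-sided 5% level, normal scores, equal SD before and after, and a before/after correlation ρ that is varied. Gains are in units of that SD.

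**Formulae.**
- True variance of the mean change: 2·SD²·(1 − ρ)/n.
- Variance that the independent test uses: 2·SD²/n.
- Ratio of standard errors, independent to true: 1/√(1 − ρ). At ρ = 0.7 this is 1/√0.3 = 1.83.
- Degrees of freedom: 2n − 2 for the independent test, n − 1 for the paired test. At n = 5 the critical values are 2.306 and 2.776, so the independent test regains a factor of 2.306/2.776 = 0.83 in interval width. At ρ = 0.7 the net ratio is about 1.83 × 0.83 = 1.52, close to the simulated 1.55.

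**Simulation of correlated pairs** (at least 200,000 replicates per row). Power is for an assumed gain of 1 SD. Width is the mean 95% CI width, independent divided by paired.

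| n | ρ | Type I error, independent | Power, independent | Power, paired | Width ratio |
|---|---|---|---|---|---|
| 5 | 0 | 5.0% | 0.29 | 0.23 | 0.86 |
| 5 | 0.3 | 2.6% | 0.26 | 0.31 | 1.02 |
| 5 | 0.5 | 1.4% | 0.25 | 0.40 | 1.20 |
| 5 | 0.7 | 0.5% | 0.24 | 0.59 | 1.55 |
| 5 | 0.8 | 0.25% | 0.24 | 0.75 | 1.88 |
| 10 | 0 | 5.0% | 0.56 | 0.51 | 0.94 |
| 10 | 0.3 | 2.3% | 0.57 | 0.66 | 1.12 |
| 10 | 0.5 | 1.0% | 0.59 | 0.80 | 1.33 |
| 10 | 0.7 | 0.2% | 0.61 | 0.95 | 1.71 |
| 10 | 0.8 | 0.06% | 0.62 | 0.99 | 2.09 |

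The paired test held its level at 4.9% to 5.1% in every row. At ρ = −0.3 the independent test rejects in 7.8% (n = 5) and 8.3% (n = 10) of trials with no true change.

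**Larger gains, ρ = 0.7, independent against paired.**
- n = 5: 0.59 against 0.89 at 1.5 SD; 0.86 against 0.99 at 2 SD.
- n = 10: 0.97 against 1.00 at 1.5 SD.

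**Low correlation.** At n = 5 and ρ = 0.2, power for a 1-SD gain is about 0.27 for both tests.

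**Signed-rank test with five pairs.** There are 2⁵ = 32 sign patterns, so the smallest exact two-sided p is 2/32 = 0.0625. The test cannot reach 0.05.

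**The case against.** **Could the sentence mean something else?** It might be read as referring to the community women, or to a comparison of change scores between groups. The first reading fails because the women's analysis has its own paragraph; the second because there is no second navigator group. Nor is this a detail left to a fuller document: the article names a specific test.

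**Does it matter for the trial?** The primary outcome is completion of screening among the community women, and no randomized comparison uses this test. With positive correlation the test is conservative, so it does not manufacture a training effect. The mean change itself is the same under either test, and descriptive statistics are planned as well. All of this stands, and it limits the severity.

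**Stronger readings to avoid.**
- A reader might infer that a real training effect will probably be missed. The article gives no gain or correlation to support that. With ten navigators and a 1-SD gain the independent test still has power of about 0.6, and with five and a 2-SD gain 0.86 at ρ = 0.7. Conversely, at n = 5, ρ = 0.5 and a 1-SD gain even the paired test reaches only 0.40, so the small number is a limit in its own right.
- A reader might say that the study's first aim is undermined. The Abstract speaks of describing how navigators are prepared and of assessing the navigation strategy. The Introduction does make the preparation something to be assessed, but the Outcome variables section ranks navigator change as secondary.
- A reader might conclude that regression must be dropped altogether. The article does not say which model is meant, and an intercept-only regression of the change scores is the paired t-test. Only a model that ignores the pairing is at fault.

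**Conclusion.** The stated test is wrong for the data described: paired scores, unpaired test, on a named secondary outcome. That follows from the text alone and needs no assumption. The size of the error does rest on assumptions, because correlation, SD and gain are all undocumented. For moderate gains with high correlation the loss of power is substantial, as the table shows; for large gains or low correlation it is small. At n = 5 and ρ of about 0.2 or less the paired test has similar or slightly lower power, because it has fewer degrees of freedom, but it still holds its level. The n = 10 figures apply only if ten navigators are both measured and trained. If ten complete the baseline questionnaire and five are trained, there are five pairs.

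This should be fixed. It is not a threat to the trial's main conclusion.

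**What to change.** In the Analysis section, for navigators only:
- Replace the independent-sample t-test with the mean within-navigator change and its 95% CI (paired t-test), and show each navigator's before and after scores.
- Do not fit a regression of score on time that ignores the pairing. If regression is kept, state the model and base it on within-navigator change.
- Do not rely on a signed-rank test if there are only five pairs.
- Describe the result as before/after change without a control group, not as an effect shown to be caused by training.

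Elsewhere:
- Put a navigator ID on both questionnaires. This must be in place before data collection, since unlinked forms cannot be paired afterwards.
- Reconcile the ten navigators under recruitment with the five under training and in the Abstract, and state how many pairs will be analysed.

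The cost is a few sentences of text and an ID field. There is no change to the randomized comparison or to the sample size of community women.

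### The assessment immediately after the education session (T1) is collected but has no stated analysis, and no main analysis is named for the secondary scale scores

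*Protocol article*

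**What the plan says.** Under Data collection and measures, the Protocol article has the community women's data "collected at baseline (T0), immediately after the intervention (T1), after 3 months (T2), and at the exit at 6 months (T3"). That section places T2 and T3 in the women's homes and gives no place for T1.

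The Analysis section names three of these four time points: "The data from the COMW at baseline, 3-month follow-up, and 6-month follow-up will be analyzed using descriptive statistics". The same sentence adds the independent-sample t-test, "linear regression, and a repeated measures ANOVA". It does not say which method answers which question or which one gives the reported effect. The section opens with "All data will be entered and analyzed in SPSS version 21 software".

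Under Outcome variables: "The secondary outcome is the change in the level of knowledge, awareness, intention, and health beliefs toward cervical cancer and screening", measured "among the patient navigators and COMW after the training and education sessions". No visit is named for it.

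Control women receive usual care only (Control group). Only intervention women are told a date and place for the intervention (Randomization).

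**The concern.** Two things look wrong.

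First, the data collection and analysis sections disagree about T1. The secondary outcome is change after the education session, and T1 follows that session most closely. By T2 and T3 the intervention women have also been offered appointment scheduling, escorting, childcare and counselling, so those visits reflect the whole package. If the analysis is run as written, the assessment nearest to the education goes unused. T1 is also defined only by reference to an intervention that control women do not receive. Unless it is given a date for them, there may be no randomised comparison at T1, and no later analysis can repair that.

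Second, three methods with different properties are listed for the same scores without a choice among them. They differ in whether and how well they use the baseline score, and in whether a woman who misses one visit stays in. At stake are precision, the number of women contributing, and the freedom to pick among several estimates of one effect.

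**Working it through.** **1. Visits, side by side**

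| Time point | Collected | Named in the analysis of community women |
|---|---|---|
| T0, baseline | yes | yes |
| T1, immediately after the intervention | yes | no |
| T2, 3 months | yes | yes |
| T3, 6 months | yes | yes |

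**2. What each listed method does with baseline and missed visits**

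- Independent t-test on follow-up scores: ignores baseline and keeps every woman seen at that visit.
- Classical repeated measures ANOVA with baseline as a time level: uses baseline through the arm-by-time term, usually less efficiently than ANCOVA, and drops any woman missing an included visit.
- Linear regression: could carry baseline as a covariate, but is not said to.

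**3. Inputs**

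The only document figure used is the sample size, 202 women (101 per arm), taken as a head count. It was checked first. A two-arm F-test "with an effect size of f = 0.3", alpha 0.05 and power 0.83 needs 97 women in total (98 balanced), so 202 is not reproduced. That is a separate matter and nothing below depends on it. The documents give no SD, baseline correlation or dropout for the scale scores. Assumed: baseline to follow-up correlation r = 0.3, 0.5, 0.7, and missingness m = 5, 10, 15% per follow-up visit. Clustering by session or navigator is left out.

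**4. Precision at one follow-up visit**

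With equal variances at both times, and in units of the follow-up-only variance, the t-test has 1, the change score 2(1 − r) and ANCOVA 1 − r².

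| r | ANCOVA vs follow-up-only: 1 − r² | ANCOVA vs change score: (1 − r²) / [2(1 − r)] = (1 + r)/2 |
|---|---|---|
| 0.3 | 0.91 | 0.65 |
| 0.5 | 0.75 | 0.75 |
| 0.7 | 0.51 | 0.85 |

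Against the follow-up-only t-test, 202 women act like 202/0.91 = 222, 202/0.75 = 269 and 202/0.51 = 396.

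The detectable difference at 83% power with 101 per arm is (1.960 + 0.954) × √(2/101) = 0.41 SD for the follow-up-only t-test. Multiplying by √(1 − r²) gives 0.39, 0.36 and 0.29 SD with ANCOVA.

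**5. Women kept by a complete-case ANOVA over T2 and T3**

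Women absent when baseline is taken are excluded (Recruitment of the COMW), so T0 should be present and losses come from follow-up.

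| m | Independent misses: 202 × (1 − m)² | Same women miss both: 202 × (1 − m) |
|---|---|---|
| 5% | 182 | 192 |
| 10% | 164 | 182 |
| 15% | 146 | 172 |

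If T1 were added to the same ANOVA under independent misses, 202 × (1 − m)³ = 173, 147 and 124 would remain. Including T1 therefore calls for a model that keeps partial data.

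**The case against.** The strongest reply is that this is a condensed article with no analysis plan shown, so covariates and missing-data rules may be set elsewhere. That stands: their absence is not counted as a fault here. What remains is what the article does state, namely a list of visits that omits one and a list of methods without a choice.

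A second reply is that all data are said to be analysed. That sentence is about software and assigns T1 no analysis. A third is that T1 may have been meant for intervention women alone, at the session, which would explain its absence from the between-arm analysis. The documents do not rule this out, so the fix allows for it.

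Several stronger readings are tempting and are not supported:

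- *The plan ignores baseline.* Baseline is a named time point, the outcome is a change, repeated measures ANOVA uses baseline through arm-by-time, and linear regression could adjust for it.
- *All the listed methods lose women with a missed visit.* A t-test at one visit keeps everyone seen then. Only the classical ANOVA deletes women listwise.
- *Adjustment is worth 96% more women.* At r = 0.7 this holds only against a follow-up-only t-test (1/0.51 = 1.96). Against a change score it is 18% (1/0.85 = 1.18).
- *The plan loses 27% of women.* That figure (1 − 0.9³) arises only if T1 enters the ANOVA, and the plan leaves T1 out.
- *The effect is largest at T1.* This is plausible, but no figure in the documents shows it. T1 is only the assessment closest to the session.

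**Conclusion.** The point holds in a limited form. The sections on data collection and analysis contradict each other on T1, and T1 has no stated timing in the control arm. Both follow from the text and need no assumption. For the secondary scores, the plan lists three methods and designates none. Two of them are weaker than a readily available alternative, and the third could be adequate but is not specified.

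The precision gain and the number of women retained are illustrations. They rest on the assumed correlations and missingness, and the retention figures are at their worst when visits are missed independently. The primary outcome, completion of screening within 6 months, is not touched. The change is worth making before data collection but does not threaten the trial's main conclusion.

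**What to change.** 1. Reconcile Data collection and measures with Analysis by naming T1 among the analysed visits.
2. State when T1 is taken in control women: in the same calendar period as the education sessions.
3. For each scale score, make one linear mixed model the main analysis, with T1, T2 and T3 as outcomes; arm, visit and arm-by-visit as fixed effects; the T0 score as covariate; and all women with at least one follow-up included. Report the arm difference at each visit. Any t-test or repeated measures ANOVA that is kept should be labelled secondary.

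Cost: mostly wording, since T0 to T3 are already planned. Control T1 assessments must be scheduled. If T1 was meant only for intervention women, this adds up to 101 control assessments. If that is not feasible, apply the same model to T2 and T3, report T1 descriptively in the intervention arm, and say so in the plan.
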